## Purpose

The purpose here is to present a protocol for a prospective longitudinal study: The Sports-Related Injuries and Illnesses in Paralympic Sport Study (SRIIPSS). In this study we will develop a web-based system that allows self-report data to be collected from Paralympic athletes. Based on these data, we will subsequently: i) record and prospectively estimate the annual incidence of sports-related injuries and illnesses among Swedish Paralympic athletes and ii) explore risk factors and mechanisms for sustaining sports-related injuries and illnesses based on athlete exposure and training loads.

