### Protocol implementation

The SRIIPSS will employ approaches similar to those that have been used in previous sports injury research [9, 23, 30, 33, 52]. It is, however, hypothesized that sports-related injuries and illnesses among Paralympic athletes differ from sport for able-bodied athletes [13, 15]. Existing research has shown that the accessibility, compatibility, interface and design of questions influence the outcome of athletes’ self-report measures [38]. Therefore, we will specifically adapt the protocol to Paralympic sport and thereafter implement the data collection.

For the data recording a commercial product for collection of survey data online (Briteback AB, Norrköping, Sweden; www.briteback.com) will be used. The research team participates in the development of the system to specifically adapt it to, for example, visually impaired athletes. The product enables definition of personal usernames and passwords to protect data from unauthorised use.

A pilot study is planned where we will enroll approximately twenty athletes with different impairments through a convenience sample from the Swedish Paralympic Program. The pilot study aims to evaluate the feasibility of the data collection system, to assure that it works for athletes with physical, visual and intellectual impairments, and to recognize and solve potential problems. The athletes will be asked to fill in the survey during 4 weeks. The pilot study period will end with a cognitive walkthrough to review the primary protocol and also validate the data. This is an evaluation method that aims to assess usability problems of a new tool early in the design process [53]. The athletes and researchers will be asked to evaluate and provide solutions for the proposed system.

Data will be collected from the end of 2016 and continue for approximately 1 year. At the start of the study the athletes fill in baseline information and a psychological profile. The athletes will thereafter be asked to report sports-related injuries and illnesses weekly. The primary outcome of the study is the incidence of injuries and illnesses, divided into a sports-related injury or illness. All data will be based on sport exposure and analyzed for the mechanism of sports-related injuries and illnesses. A closure form will be used when the athlete is back in full training following an injury or illness (Table 2).

**Table 2 Tab2:** Overview of the outcome measures of the SRIIPSS

Outcome measure	Parameter	Measurement

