### Statistical analysis plan

The primary variables for the descriptive analyses are records of the incidence of sports-related injuries and illnesses, i.e., recordings of injury or illness events that are conditioned on that the participant is ‘healthy’ at the start of data collection period. Incidences will be calculated separately for injuries and illnesses. The incidence rates will be calculated as the number of new incidents divided by total athlete exposure hours (per 1000 h of sport participation). Health-incidents not related to sport will be analyzed separately. All events will be evaluated according to the mechanism of sports-related injuries and illnesses (independent variables). The data will be assessed for normality and will be presented using quantitative descriptive statistics (mean, median, standard deviation, minimum and maximum for continuous data and frequency and proportion (%) for categorical data). Differences in proportions between different categories (e.g., age-groups, gender, impairments, previous injury, competition frequency and level of severity of impairment) will be analyzed as covariates using chi-square statistics. The primary end point for the injury risk analyses will be time to injury. The incidence data will be further analyzed with the Kaplan-Meier survival analysis method, the log-rank test and Cox proportional hazards regression. To analyze the relationship between training loads and injury and illness incidence, Pearson product moment correlation coefficients will be used. A significance level of 0.05 and 95 % confidence intervals will be used in all tests. The data will be analyzed using IBM SPSS Statistics version 23.

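### The listed risk factors are assigned to chi-square tests of proportions, which take no covariates and ignore exposure hours, while the planned Cox regression is not tied to those factors or to an exposure time scale

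*Protocol article*

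**What the plan says.** All places are in the protocol article.

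- **Incidence measure** (Statistical analysis plan): "The incidence rates will be calculated as the number of new incidents divided by total athlete exposure hours (per 1000 h of sport participation".
- **Group comparisons** (same section): "Differences in proportions between different categories (e.g., age-groups, gender, impairments, previous injury", and then "competition frequency and level of severity of impairment) will be analyzed as covariates using chi-square statistics".
- **Risk analysis** (the two sentences after that): "The primary end point for the injury risk analyses will be time to injury" and "The incidence data will be further analyzed with the Kaplan-Meier survival analysis method, the log-rank test and Cox proportional hazards regression". Neither sentence names covariates or a time scale.
- **Principle** (Protocol implementation): "All data will be based on sport exposure and analyzed for the mechanism of sports-related injuries and illnesses".
- **Aim ii** (Purpose): risk factors and mechanisms are to be explored "based on athlete exposure and training loads".
- **Data** (Athlete weekly e-diary): the amount of training and competition is reported each week, so hours per athlete will be available.

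**The concern.** The sentence on group comparisons cannot be carried out as written. A chi-square test compares proportions across the categories of one factor. It does not adjust for anything, so nothing can enter it as a covariate.

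It also leaves the plan's own scale. Incidence is defined per hour of sport and the risk-factor aim is tied to exposure, but a proportion has no hours in its denominator. Two groups with the same hourly risk and different training volume have different expected proportions injured. Two groups with different hourly risk can have the same proportion. Competition frequency, one of the listed factors, is itself a component of exposure, so for that factor confounding with hours is close to built in.

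At stake is which factors the study reports as risk factors, and so which groups later preventive work would target.

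**Working it through.** **No figure to reproduce.** The article states no power, effect size or expected event count. Its number of athletes, about 100, is a total population and not a calculated sample size. It gives no injury rate and no hours by group. The calculation below is therefore an illustration under stated assumptions.

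**Inputs**
- From the article: about 100 athletes, about 1 year of follow-up, significance level 0.05 (two-sided assumed).
- Assumed: two groups of 50; the same true hourly rate in both (1, 2 or 4 per 1000 h); Poisson events; annual hours as shown; the proportion tested is athletes injured at least once.

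**Formulas**
- Proportion injured: p = 1 − exp(−rate × hours).
- Rejection probability: Φ{ (|p₂ − p₁| − 1.96 √[2p̄(1 − p̄)/50]) / √[(p₁(1 − p₁) + p₂(1 − p₂))/50] }, where p̄ is the mean of p₁ and p₂.

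Example at 2 per 1000 h and 200 vs 400 h: p₁ = 1 − exp(−0.4) = 0.330 and p₂ = 1 − exp(−0.8) = 0.551, so the rejection probability is 0.607.

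| Rate per 1000 h | Hours per year | Proportion injured | Apparent risk ratio | Chi-square rejects |
|---|---|---|---|---|
| 1 | 200 vs 400 | 18.1% vs 33.0% | 1.82 | 40% |
| 2 | 200 vs 400 | 33.0% vs 55.1% | 1.67 | 61% |
| 4 | 200 vs 400 | 55.1% vs 79.8% | 1.45 | 76% |
| 1 | 400 vs 500 | 33.0% vs 39.3% | 1.19 | 10% |
| 2 | 400 vs 500 | 55.1% vs 63.2% | 1.15 | 13% |
| 4 | 400 vs 500 | 79.8% vs 86.5% | 1.08 | 14% |

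The true hourly rate ratio is 1.0 in every row.

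**Check by simulation** (4000 runs, no continuity correction). At 200 vs 400 h, chi-square rejects in 38%, 64% and 77% for the three rates. A Poisson rate test on the same data, using hours, rejects in 5.1%, 5.5% and 4.4%. With 300 h in both groups at 2 per 1000 h, chi-square rejects in 5.6%. The excess comes from the hours gap alone.

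**Masking.** A group at 4 per 1000 h with 200 h expects 0.8 injuries per athlete. A group at 2 per 1000 h with 400 h also expects 0.8. Both show 1 − exp(−0.8) = 55.1% injured, although the hourly rates differ twofold.

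**Does the planned Cox model remove the problem?** Only if exposure enters it. On calendar time, with equal hourly risk and 200 vs 400 h, the hazard ratio is 400/200 = 2.0. Expected events are 50(p₁ + p₂) = 25.5, 44.0 and 67.4. The rejection probability Φ(√events × ln 2 / 2 − 1.96) is 42%, 63% and 81%.

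**The case against.** A reader who looks only at the chi-square sentence might infer that chi-square is the plan's risk analysis, that aim ii therefore has no suitable method, and that groups that train more will appear to be at higher risk. The article does not support that, for these reasons:

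- **Cox regression is planned.** The next two sentences make time to injury the primary end point for injury risk and name Cox regression, which accepts covariates and handles unequal follow-up. Rates per 1000 h are also computed. This stands.
- **The distortion is conditional.** It needs an hours gap between the groups compared, and the article reports no hours by group. With a modest gap it is small. This stands.
- **The proportion is not defined.** The sentence follows the descriptive statistics and could concern ever-injured athletes or the distribution of onset, type or severity. For a purely descriptive distribution, chi-square is acceptable. This stands. It is a reason to limit the sentence to that use.
- **The annual difference is real.** At equal hourly risk, athletes who train twice as much do have more injuries per year. This is true, but that is not the per-hour scale on which the plan defines incidence.
- **Model detail belongs in a fuller analysis plan.** It is no fault that an article leaves out the Cox time scale and covariates. The silence does mean that the Cox sentence cannot be taken to correct the explicit assignment of the listed factors to chi-square. The survival sentence speaks of incidence data generally, but the time-to-event end point is named for injury only, so illness has no clearly stated exposure-based group comparison.

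**Conclusion.** The point holds in a limited form. The sentence that assigns the listed factors to chi-square as covariates is wrong as written and departs from the plan's own exposure-based measure and aim. Chi-square is not the only risk analysis, but nothing stated places these factors in an exposure-based model.

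With 50 athletes per group, equal hourly risk and 1 to 4 injuries per 1000 h, false rejection is about 40–76% at a twofold hours gap, 10–14% at 400 vs 500 h, and about 5% with equal hours. These figures rest on assumed rates, hours and group sizes, on Poisson events, and on ever-injured as the tested outcome. The mismatch between test and measure does not depend on them; its practical size does.

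**What to change.** 1. Limit chi-square to descriptive distributions such as type, onset and severity, with exact tests where cells are sparse. Sparse cells are likely by impairment: ten types, 100 athletes evenly spread and an assumed 70% injured give 100/10 × 0.30 = 3 expected uninjured athletes per type. Drop the reference to covariates from that sentence.
2. For risk-factor inference, report rate ratios with 95% confidence intervals from a negative binomial or Poisson-GEE regression of incidents per athlete, with log(exposure hours) as offset, separately for injury and illness. Both allow for more variation between athletes than a plain Poisson model.
3. In addition or instead, run the planned Cox model on cumulative exposure hours. If repeat injuries count, use an Andersen-Gill or frailty form.
4. Prespecify a small covariate set, one factor at a time or a few together, with impairment types collapsed. Entering all six listed factors at once with about 100 athletes would overfit.

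The cost is revised wording and slightly more analysis work. No new data are needed. The limitation is that multivariable adjustment will stay modest at this sample size. Whether hours are the right denominator for illness is a separate question, and this change keeps the one the plan states.

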### Setting and participants

Potential participants will be recruited through the Swedish Paralympic Program, which covers candidates for the Summer and Winter Paralympic Games. The total number of athletes in the Swedish Paralympic program is around 100. All potential participants will be invited by post or email. They will receive information about the proposed study, a request for a contact e-mail and phone number, a consent form for participation and a prepaid return envelope. To be eligible for the study the athlete should belong to one of the ten eligible impairment types, according to the IPC classification system, and participate in either a Paralympic summer or winter sport (Table 1). The following inclusion criteria will be used: age 18–55 years, being a registered athlete within the Swedish Paralympic Program, being able to communicate in Swedish and having the opportunity to respond weekly to a web-based questionnaire. As the number of Swedish Paralympic athletes is small and this is an understudied topic, a total population design will be applied.

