### Definitions of injury and illness

The main injury definition in the SRIIPSS follows, with some alterations, the definitions previously used for soccer, rugby union, the Olympic Games and athletics [27, 29, 30, 52]:*Any new musculoskeletal pain, feeling or injury that result from participation in Paralympic sport (training or competition) and cause changes in normal training/competition to the mode, duration, intensity or frequency, regardless of whether or not time is lost from training or competition.*

An illness including psychological complaints will be defined as:*Any new illness or psychological complaint that cause changes in normal training/competition to the mode, duration, intensity or frequency, regardless of whether or not time is lost from training or competition.*

The reported incidents will be categorized as ‘sudden onset’ or ‘gradual onset’. A sudden onset incident refers to an incident caused by a specific identifiable episode resulting in a rapid onset of experienced distress. Subsequently, sudden onset injuries will be categorized according to the cause of the incident as: i) traumatic injuries – a condition caused by an identifiable single external transfer of energy (for example, a bone fracture caused by a fall or a ligament tear caused by contact with an obstacle), or ii) overuse injuries – a condition to which no identifiable single external transfer of energy can be associated (examples of overuse sudden onset injuries include tendon tears).

A gradual onset incident refers to a condition that manifests itself over a period of time, or when there is a gradual increase in the intensity of experienced distress, without a single identifiable event being responsible for the condition. Examples of gradual onset conditions include overtraining syndromes and overuse injuries, such as tendinosis and tendinopathies [52].

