The arguments for using these definitions are based, first, on that the incidents will be recorded from the athlete’s own subjective perspective, feelings and experiences of pain, injury and illness. Second, these definitions support the concept of partial time-loss injury [33, 54]. In order to capture these injury events it is important to identify complex background patterns for overuse injuries [33, 34]. Third, this athlete population already has an existing impairment and is exposed to elements not present in abled-bodied athletes. To allow for a better understanding of sports-related injuries and illnesses in this population, we believe that it is important to assess various factors such as pain, injuries, illnesses, and psychological stressors in order to obtain a comprehensive picture of Paralympic athletes’ health. To allow comparisons with previous studies of Paralympic athletes and non-disabled athletes, the incidents will at a secondary level of the analysis be identified by time-loss and tissue damage.

In agreement with previous injury surveillance studies [28, 52] a recurrent condition will be defined as:*An incident of the same type and at the same site linked to an index incident and which occurs after an athlete’s return to full function and participation (“full recovery”) from the index recordable incident.*

The incidents will be subcategorized into re-injuries and exacerbations. Categorization of subsequent injuries – new, recurrent, exacerbation or multiple – will be taken into account using the Subsequent Injury Categorization (SIC) model before analysis [55].

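### Injury risk is analysed as time to injury with single-event methods, without saying first or every injury, although the protocol foresees repeat injuries in one athlete

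*Protocol article*

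**What the plan says.** The risk endpoint is given in one sentence of the Statistical analysis plan: "The primary end point for the injury risk analyses will be time to injury". The methods follow: "The incidence data will be further analyzed with the Kaplan-Meier survival analysis method, the log-rank test and Cox proportional hazards regression". Neither sentence says whether an athlete contributes one injury or all of them. No frailty term, robust variance or recurrent-event model is named.

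Other sections set up data in which repeats can occur:

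- Protocol implementation: "The athletes will thereafter be asked to report sports-related injuries and illnesses weekly", over a period of about one year ("Data will be collected from the end of 2016 and continue for approximately 1 year"). A closure form marks the return to full training.
- Definitions of injury and illness: the injury definition is broad. It takes in any new pain, feeling or injury that alters training, with or without lost time. A recurrent condition is defined against an index incident, and subsequent injuries "will be taken into account using the Subsequent Injury Categorization (SIC) model before analysis".
- Statistical analysis plan: the incidence rate puts all new incidents over total exposure hours.

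On size, Setting and participants says "The total number of athletes in the Swedish Paralympic program is around 100" and that "a total population design will be applied".

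**The concern.** Kaplan-Meier, log-rank and ordinary Cox are built for one event per subject. Because the endpoint is not defined further, the plan can be read in two ways.

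- **First injury.** The analysis is sound, but later injuries, including every recurrence that the protocol takes care to classify, play no part in the search for risk factors.
- **Every injury.** Injuries from one athlete enter as if they came from different athletes. If athletes differ in underlying risk, standard errors are too small and chance differences look significant. The Discussion itself hypothesizes that injuries and illnesses may be specific to sport and impairment type, so some heterogeneity is expected.

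The subsequent-injury categorization does not settle this. It labels how incidents relate to one another before the analysis; it does not make the models that follow allow for dependence.

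At stake is the second aim, risk factors, in a cohort that cannot be enlarged because it is already the whole programme.

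**Working it through.** The protocol states no expected injury rate, event count or power, so there is no figure of its own to reproduce. What follows is an illustration.

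**Inputs from the protocol.** n = 100 athletes (Setting and participants); follow-up of 1 year (Protocol implementation); significance level 0.05 and 95% intervals (Statistical analysis plan), taken as two-sided.

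**Assumed.** Mean injuries per athlete-year μ = 0.5, 1, 2 or 3 (injuries only, not illnesses). Gamma-distributed athlete risk with variance θ = 0, 0.5 or 1.

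**Reading 1: first injury only.** The probability of no injury is P0 = exp(−μ) if θ = 0, otherwise (1 + θμ)^(−1/θ). First injuries = 100 × (1 − P0). Unused share = 1 − (1 − P0)/μ. Example with μ = 2, θ = 0.5: P0 = 2^(−2) = 0.25, so 75 first injuries out of 200, and 62.5% are unused.

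| μ | First injuries (θ = 0 / 0.5 / 1) | Unused share, θ = 0 to 1 |
|---|---|---|
| 0.5 | 39 / 36 / 33 of 50 | 21–33% |
| 1 | 63 / 56 / 50 of 100 | 37–50% |
| 2 | 86 / 75 / 67 of 200 | 57–67% |
| 3 | 95 / 84 / 75 of 300 | 68–75% |

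More than half are unused only above about 1.6 injuries per athlete-year (θ = 0), 1.24 (θ = 0.5) or 1.0 (θ = 1).

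**Unused injuries are not the same as lost information.** Repeat injuries in one athlete are partly redundant. For a fixed athlete-level covariate, all injuries analysed with correct variance are worth about 100μ/(1 + θμ) independent events. At μ = 2 this is 200, 100 and 67 for θ = 0, 0.5 and 1, against 86, 75 and 67 first injuries. With power = Φ(√(d/4) × ln 1.5 − 1.96) for a hazard ratio of 1.5 and a 50:50 covariate:

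- θ = 0: 47% with first injuries, 82% with all.
- θ = 0.5: 42% (√18.75 × 0.405 − 1.96 = −0.20) against 53%.
- θ = 1: 38% for both.

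This count leaves out two things: under heterogeneity the first-injury hazard ratio is pulled towards 1, and covariates that change within an athlete behave differently.

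**Reading 2: every injury, treated as independent.** The variance is understated by the factor 1 + θμ. Actual coverage = 2Φ(1.96/√(1 + θμ)) − 1.

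| μ | θ = 0 | θ = 0.5 | θ = 1 |
|---|---|---|---|
| 1 | 95% | 89% | 83% |
| 2 | 95% | 83% | 74% |
| 3 | 95% | 78% | 67% |

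The formula carries over to Cox. If all athletes are followed for the full year and stay in the risk set, a Cox model on all injuries with one 50:50 athlete-level covariate gives exactly the log ratio of the two injury counts, with naive standard error √(1/a + 1/b), where a and b are those counts.

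Simulating that analysis with no true effect (4,000 replicates per setting) gave these false-positive rates:

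- naive, μ = 1 to 3: 0.11–0.21 at θ = 0.5, 0.16–0.33 at θ = 1, and about 0.05 at θ = 0;
- athlete-clustered standard errors: 0.05–0.065 throughout.

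**The case against.** The case for leaving the text alone has real parts. Time to first injury is a legitimate endpoint. It fits the plan's conditioning on the participant being healthy at the start, and later incidents still count in the primary outcome, the incidence rate. Under strong heterogeneity the first-injury analysis loses little for fixed covariates. Covariates such as impairment or previous injury would also absorb part of the heterogeneity if entered in the Cox model. The text is a journal article, and the variance estimator could sit in a fuller plan. All of this stands and limits the size of the point. It does not remove it, because the article itself fixes the endpoint and the methods and leaves the reading open.

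Three stronger readings are tempting and are not supported:

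- *That athletes will have several injuries a year, so most are discarded.* Weekly reporting and a broad definition make repeats possible; no rate is given. At 0.5 per athlete-year, 21–33% are unused.
- *That the Cox model is not tied to exposure hours.* The time scale is unstated, and Protocol implementation says that all data will be based on sport exposure. Silence is not a choice of calendar time.
- *That training load is wrongly entered in Cox as a fixed covariate.* The plan assigns load to Pearson correlation and never places it in the Cox model.

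**Conclusion.** The point holds in a limited form. The protocol foresees repeat injuries, names single-event methods for injury risk, and does not say which injuries enter. On the first-injury reading there is no bias of principle, only an analysis that leaves 21–75% of injuries unused over the assumed range; the loss of information is smaller and can be nil at frailty variance 1. On the every-injury reading, intervals are too narrow if athletes differ in risk: about 83% coverage at 2 injuries per year and frailty variance 0.5, and no error at variance 0.

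The same inflation would apply to incidence-rate intervals if they were computed as simple Poisson intervals, but the text does not give their method. Every figure rests on the assumed injury rate and frailty variance.

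**What to change.** In the Statistical analysis plan:

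1. Say that Kaplan-Meier and log-rank describe time to first injury.
2. Add a recurrent-event model for all injuries. Suitable choices include Andersen-Gill or gap-time Cox with athlete-clustered robust variance or frailty, or negative-binomial rates with exposure hours as offset.
3. Take the athlete out of the risk set during an injury and back in at the return to full training, using the closure form.
4. State how the subsequent-injury categories enter, for example whether exacerbations count as new events.
5. Compute incidence-rate intervals with allowance for clustering by athlete.

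The weekly diary and closure form already collect what is needed. The cost is plan wording, a little more programming, and possibly a second package beside SPSS version 23.
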